## Abstract

**Background:**

Incidence of end stage kidney disease (ESKD) for Indigenous Australians is especially high in remote and very remote areas of Australia (18 and 20 times the rate of comparable non-Indigenous people). Relocating away from family and country for treatment, adjusting to life with a chronic condition and time lost to dialysis cause grief and sadness which have immense impact on quality of life and challenges treatment adherence. We describe the first randomised controlled trial to address both chronic disease and mental health in Indigenous people with ESKD, which is the first to test the effectiveness of a culturally adapted e-mental health intervention in this population. It builds on an existing program of mental health research with demonstrated efficacy – the Aboriginal and Islander Mental Health Initiative (AIMhi) – to test the newly developed electronic motivational care planning (MCP) therapy – the AIMhi Stay Strong App.

**Methods:**

This is a 3-arm, waitlist, single-blind randomised controlled trial testing the efficacy of the Stay Strong App in improving psychological distress, depressive symptoms, quality of life and treatment adherence among Indigenous clients undergoing haemodialysis for ESKD in Alice Springs and Darwin with follow up over two periods of 3 months (total of 6 months observation). The study compares the efficacy of MCP using the AIMhi Stay Strong App with two control groups (control app intervention and treatment as usual) on participant-reported psychological distress (the primary outcome) using the Kessler Distress Scale (K10); depressive symptoms using the adapted Patient Health Questionnaire (PHQ-9); quality of life using the EuroQoL instrument (EQ5D) and adherence to dialysis treatment planning through file audit. Participants are randomised to receive MCP either at baseline (early treatment) or after 3 months (delayed treatment). The study also examines the cost effectiveness of this therapy in this setting through examination of health care service utilisation across groups during the first 3 months.

**Discussion:**

This project will contribute much needed evidence on the efficacy of an electronic wellbeing intervention for Indigenous people with ESKD – a group in which distress is likely to be unacceptably high, yet relatively untreated.

**Trial registration:**

Australian New Zealand Clinical Trial Registry; ACTRN12617000249358; Date registered: 17/02/2017.

## Background

The incidence of end stage kidney disease (ESKD) for Indigenous Australians in the Northern Territory (NT) is 15.3 times the rate of non-Indigenous Australians, with the burden of the disease on the increase (96% increase in Indigenous incidence nationally over the 1991–2010 period) [1]. People with ESKD require renal replacement therapy (regular dialysis or kidney transplant) to survive. Such treatments are resource intensive adding to an already high burden for the individual and health care system.

People with chronic kidney disease (CKD) sustain many losses - physical functions, cognitive abilities, and role in the family and workplace [2], and depression is common in those undergoing dialysis (25% with depressive symptoms when assessed by clinical interview, 40% when assessed by self-report measures) [3]. These levels are unacceptably high given that depressive symptoms are a risk factor for poor outcome in people with ESKD on dialysis [4].

Early intervention for psychological distress among people with CKD has the potential to prevent or defer onset of chronic and debilitating mental disorders and minimise the impact of wellbeing concerns on adherence and treatment outcomes. Meta-analyses estimate reductions in incidence of depression of approximately 20% when preventative interventions are delivered to the general population with no diagnosed depression at baseline [5, 6].

Despite recognition that psychosocial factors are associated with morbidity and mortality in many chronic conditions, including CKD, well-designed intervention studies are lacking [2, 4]. The most recent Cochrane Review (2005) failed to identify any randomised controlled trials (RCTs) assessing psychosocial interventions for depressed people on dialysis [7]. Furthermore, there is a significant lack of rigorous effectiveness trials for mental health interventions in an Indigenous context generally [8]. Given the scarcity of evidence, RCTs in this area are desperately needed [4].

One of the very few formally evaluated, culturally-adapted, mental health and chronic disease self-management interventions for Indigenous people was developed through the Aboriginal and Islander Mental Health Initiative (AIMhi). Assessment, psycho-education, and care-planning resources were developed following extensive consultation and collaboration with local Aboriginal mental health workers (AMHW) through exploration of local Indigenous perspectives of mental health and with recognition of the holistic nature of wellbeing [9–11]. ‘Motivational care planning’ (MCP) combines problem solving therapy and motivational interviewing, to create a ‘low-intensity’ treatment that differs from established approaches by utilising a holistic, strengths-based approach with pictorial tools [10, 12]. It was evaluated in one of the first successful NHMRC-funded RCTs assessing mental health interventions in a remote Indigenous context, with further qualitative studies and evaluations confirming acceptability and feasibility [9, 11, 13, 14]. The RCT showed that the MCP intervention resulted in significant improvements in well-being, life skills, and alcohol dependence among Indigenous clients with chronic mental illness, with changes sustained over 18 months [9].

MCP is a theoretically sound, evidence-based approach to comorbidity, which has been used in settings other than mental health including substance misuse, gambling and chronic disease self-management [13–15]. The therapy adopts an empowering, person-centred, holistic and strengths based perspective which acknowledges and promotes Indigenous cultural and family values and client self-management [16]. The AIMhi MCP intervention has recently been translated into a digital (tablet) format (the AIMhi Stay Strong App), making it even more interactive and visually appealing. The result is the first available e-mental health approach developed specifically for Indigenous Australians.

This study examines the 3- and 6-month impact and cost effectiveness of the MCP therapy delivered by the AIMhi Stay Strong App for improving mental health and wellbeing in a renal dialysis setting, relative to two control conditions.

## Methods

### Aims

The primary aim of the study is to determine whether MCP using the AIMhi Stay Strong App reduces psychological distress for Indigenous people receiving haemodialysis, relative to delayed-treatment control groups at 3 months, and whether benefits are maintained at 6 months post-recruitment. Secondary aims test the impact of MCP using the AIMhi Stay Strong App in improving depressive symptoms, Quality of Life (QoL) and dialysis treatment adherence. We also aim to examine the cost effectiveness of this therapy.

We hypothesise that MCP therapy using the AIMhi Stay Strong App will be cost-effective and superior to both a contact control using another app (Hep B Story) [17] and usual care, in reducing psychological distress and depressive symptoms, and improving quality of life and dialysis treatment adherence at 3 months. We expect that MCP that is received in the control groups after the 3-month assessment will result in those groups showing improvements in these outcomes between 3 and 6 months.

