#### Contact control/delayed treatment- (CC/DT)

##### Baseline

Participants who are randomised to CC/DT receive 20 min of contact with the researcher using a culturally appropriate generic health App (i.e. The Hep B Story) at baseline, with a further 20-min session using the same app after 2–4 weeks. Session 1 of CC/DT goes through the structured Hep B App. Discussions specifically avoid review of family, strengths or individual goal setting. The participant interacts with the App with support from the researcher, and discussion focuses on navigation of the App and the App content. A ‘goal’ is agreed to talk to someone else in their family about the app content before the next session. A pictorial summary (utilising similar colours and images to the intervention summary) is given to the client. Session 2 reviews the information discussed in Session 1. This ensures each group receives the same contact time with researchers and interaction based on a structured App to aid participant blinding and to structure the control session. Participants receive a text message or phone call with a health tip linked with the health App in the intervening weeks.

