### Sample size and power

We will recruit 156 participants over 15 months, allowing for up to 10% drop out at 6 months. With a SD of 8.5 for the baseline score and a sample of 62, 62 and 32 participants per arm, we will be able to detect a minimum difference between the group mean scores equal to 5 at 3 months with 90% power and an alpha of .05. This sample size will also give over 90% power to detect a minimum change in mean score within groups equal to 5. This calculation allows for 10% attrition. We consider a difference between the group mean scores of 5 to be clinically significant. A change of this magnitude (effect size = 0.6) suggests that the change would be positive for approximately 73% of the population.

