#### Primary endpoint analyses

Continuous outcome measures will be compared between the three groups using a linear mixed effect model, with transformations applied to the outcome measure if not normally distributed. The mixed effect models with random effect intercept will allow for correlation between measurements of K10 scores taken at three points in time within the same subject, and will estimate the effect of the interventions at 3 and 6 months. All analyses will be conducted on an intention-to-treat basis. Preliminary analyses will check for group differences at baseline and control for them statistically if necessary.

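### The hypothesis needs MCP to beat both controls at 3 months, but the stated 90% power fits neither MCP v TAU (77%) nor both together (72%, or 67% after 10% attrition)

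*Protocol article*

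**What the plan says.** The protocol article describes the comparison that decides the trial in three ways.

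- **Aims, primary aim:** the effect of MCP on distress is judged "relative to delayed-treatment control groups at 3 months, and whether benefits are maintained at 6 months post-recruitment". The two control arms are neither separated nor ranked.
- **Aims, hypothesis:** MCP will be "superior to both a contact control using another app (Hep B Story) [17] and usual care, in reducing psychological distress and depressive symptoms", with 3 months as the time point.
- **Primary endpoint analyses:** "Continuous outcome measures will be compared between the three groups using a linear mixed effect model", and the model "will estimate the effect of the interventions at 3 and 6 months".

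The Sample size and power section gives one between-group statement: with SD 8.5 and arms of 62, 62 and 32 the trial can "detect a minimum difference between the group mean scores equal to 5 at 3 months with 90% power and an alpha of .05". It adds that 10% attrition is allowed for and justifies the target as follows: "We consider a difference between the group mean scores of 5 to be clinically significant". It does not say which two means, or which overall test, the 90% refers to. Under Randomisation the allocation is 1:1:0.5, so TAU is about half the size of the other two arms.

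**The concern.** With one arm half the size of the others, a single power figure cannot hold for both pairwise contrasts. A hypothesis that requires both contrasts to succeed has less power than the weaker of the two. A reader who puts the hypothesis beside the sample size would conclude that the trial has a 90% chance of showing superiority to both controls if the true benefit is 5 points against each. If that chance is nearer 70%, a trial of an intervention that works as hoped would fail its own hypothesis roughly three times in ten.

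The two controls also answer different questions. Under Contact control/delayed treatment, the comparison app equalises researcher contact and provides "interaction based on a structured App to aid participant blinding and to structure the control session". TAU participants receive only the questionnaires at baseline. Beating TAU but not the contact control would be compatible with an effect of attention, so it matters which contrast the trial is sized for.

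**Working it through.** **Inputs (Sample size and power section).** Difference 5 points; SD 8.5; alpha .05 (sidedness not stated, two-sided assumed); arms 62/62/32, which sum to the 156 to be recruited. Ten percent attrition gives 62 × 0.9 = 55.8 and 32 × 0.9 = 28.8, so about 56/56/29.

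**Formula for one contrast (normal approximation).** SE = SD × √(1/n₁ + 1/n₂); power = Φ(5/SE − 1.96).

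**Step 1. Reproduce the 90%: MCP v contact control, 62 v 62.**
SE = 8.5 × √(2/62) = 1.527; 5/1.527 = 3.275; Φ(1.315) = 90.6% (90.1% with the t distribution). An overall three-group F test with MCP 5 points below both controls also gives 90.1%. Both use every recruited participant, with no attrition removed.

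**Step 2. MCP v TAU, 62 v 32.**
SE = 8.5 × √(1/62 + 1/32) = 1.850; 5/1.850 = 2.703; Φ(0.743) = 77.1%.

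**Step 3. Both contrasts significant.** They share the MCP arm, so their test statistics are correlated:
ρ = (1/62) / √[(1/62 + 1/62)(1/62 + 1/32)] = 0.01613/0.03909 = 0.413.
Power for both is the bivariate normal probability that both statistics exceed 1.96, with means 3.275 and 2.703 and correlation 0.413. This gives 72.4%.

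**Step 4. After 10% attrition, 56/56/29.**
MCP v contact control: SE = 8.5 × √(2/56) = 1.606; Φ(3.113 − 1.96) = 87.5%.
MCP v TAU: SE = 8.5 × √(1/56 + 1/29) = 1.945; Φ(2.571 − 1.96) = 72.9%.
Both: 67.1%.

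| Two-sided .05, true difference 5 | 62/62/32 | 56/56/29 |
|---|---|---|
| MCP v contact control | 90.6% | 87.5% |
| Overall three-group F test | 90.1% | 86.6% |
| MCP v TAU | 77.1% | 72.9% |
| Both controls beaten | 72.4% | 67.1% |

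**Step 5. Sensitivity to baseline adjustment.** With baseline K10 as a covariate the residual SD is 8.5 × √(1 − r²). The protocol gives no r, so these values are assumptions:

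| Assumed r | Both, 62/62/32 | Both, 56/56/29 |
|---|---|---|
| 0.3 | 77% | 72% |
| 0.5 | 86% | 81% |
| 0.6 | 91% | 88% |
| 0.7 | 96% | 94% |

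**Step 6. Sensitivity to sidedness.** At one-sided .05 with 62/62/32, MCP v TAU has 85.5% and both 82.4%. With 56/56/29, both has 78.3%. None reaches 90%.

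**The case against.** **The article may simply not name its contrast.** A condensed protocol article can leave contrasts and testing order to the analysis plan or full protocol, neither of which is shown. This stands: a missing testing order alone would be no finding. What remains is inside the article, where the hypothesis and the power figure do not match.

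**The 90% may refer to a three-group test or to pooled controls.** The article does not say that the calculation is pairwise, and the overall test does give 90.1%. The primary aim could also be read as MCP against the two controls combined, which would have 94.9% power at full enrolment and 92.8% after attrition. Both readings are possible, but neither test establishes superiority to each control separately. The overall test has the same 90.1% power when the contact control alone is 5 points worse and MCP equals TAU.

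**67% is the low end.** The 10% loss is given as an upper limit at 6 months, so less may be lost by 3 months, and use of baseline scores could raise power. This stands in part. The figure for both is best given as 67% to 72% without baseline gain. Exceeding 90% needs an assumed correlation of about 0.6 at full enrolment, or between 0.6 and 0.7 after attrition. The power section claims no such gain.

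**Stronger readings that the article does not support.**

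- A reader might infer that the type I error is inflated. Two unadjusted two-sided .05 tests give a 9.3% chance of at least one false positive (4.6% for false superiority, against 2.5% for one test). This applies only if beating either control counted as success, and no section says so. If both must succeed, no adjustment is needed.
- A reader might count the 6-month estimates as further superiority tests. The Aims place superiority at 3 months, and both control arms receive MCP after that assessment.
- A reader might infer that the single-blind label is valid only against the contact control. The article says the control app helps participant blinding, but not who is blinded, so it gives no basis for restricting the label.

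**Conclusion.** The concern holds as a mismatch between the hypothesis and the power statement. The 90% is right for MCP v contact control, or for an overall three-group test, with all 156 participants analysed. It overstates power by about 13 percentage points for MCP v TAU (77.1%) and about 18 for beating both controls (72.4%). After the attrition that the section says is already allowed for, the shortfalls are about 17 points (72.9%) and 23 points (67.1%).

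These figures assume two-sided .05, a common SD of 8.5 at 3 months, a true 5-point difference against each control, and no gain from baseline K10. With an assumed correlation of 0.5 and baseline as a covariate, power for both is about 81% after attrition, still below 90%. The result does not show that the planned analysis is invalid or that its type I error exceeds .05.

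**What to change.** **Sample size and power.** State that the 90% refers to MCP v contact control on K10 at 3 months with 62 per arm, if that is what was calculated. Add the power for MCP v TAU and for both contrasts, with and without 10% attrition, as in the first table above. If a gain from baseline K10 is relied on, state the assumed correlation and its source.

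**Aims and Primary endpoint analyses.** Fix the order for K10 at 3 months:

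1. MCP v contact control at two-sided .05 is the primary test.
2. MCP v TAU is tested at two-sided .05 only if the first test succeeds.
3. Superiority to both is claimed only if both tests succeed.

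This gives full alpha to the contrast that reproduces the 90% and keeps the familywise error for the two contrasts at .05.

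**Cost.** About a paragraph of wording and no extra participants. The stated power becomes less favourable, and there is no confirmatory claim against TAU if the first test fails. The sequence does not raise the power to beat both controls, which stays at 67% to 72% on the protocol's inputs. For that reason the power figures must be restated as well as the order fixed.

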### Study design

This is a 3-arm, waitlist, single-blind randomised controlled trial testing the efficacy of the Stay Strong App MCP intervention in improving wellbeing among Indigenous clients undergoing haemodialysis for ESKD in Alice Springs and Darwin, with assessments at Baseline, 3 and 6 months (see Fig. 1 for participant flow). The three treatment conditions are: 1) Early treatment with MCP using the Stay Strong App 2) Contact control/Delayed treatment with the Stay Strong App (i.e. patients are engaged with the researcher for a similar time using an electronic application addressing general health issues) and 3) Treatment as usual/Delayed treatment with the Stay Strong App (see Fig. 1).

**Fig. 1 Fig1:**
[figure not shown]
Participant Flowchart

### Participants and setting

Indigenous people presenting to participating haemodialysis services in Alice Springs and Darwin – Western Desert Nganampa Walytja Palyantjaku Tjutaku (WDNWPT), Central Australian Renal Services, and Top End Renal Services, are approached to provide informed consent. Approximately 80% of participants are expected to speak English as a second or third language. Inclusion criteria include identification as an Aboriginal and/or Torres Strait Islander person and aged ≥18 years, currently receiving maintenance haemodialysis in Alice Springs or Darwin and having been receiving this treatment for more than 6 months. Exclusion Criteria are aged < 18 years, guardianship order in place, or inability to provide informed consent (e.g. because of cognitive or visual impairment). Whether potential participants meet criteria for inclusion is determined through liaison between project staff and the patient’s care coordinator.

### Consent and culturally appropriate approach

Research officers use pictorial information sheets and flipcharts, screening and intervention tools which use plain English and are available in 11 NT Aboriginal languages, to assist understanding. Participants are offered communication support (interpreters, translators, language recordings). Demographic information and outcome measures are collected using a tablet device that includes pictorial prompts and Aboriginal language recordings for each item (choice of 11 NT languages). Interpreters are also utilised where necessary. Assessment and treatment sessions occur at a place that is identified by the participant as most comfortable for them, which may be outdoors, at the clinic, while receiving dialysis, or at their accommodation.

### Randomisation

Eligible participants are randomised following baseline assessment using a block sequential random number sequence and an envelope system of randomisation, stratified by site, level of psychological distress (high or low) and access to respite dialysis in home community. An independent statistician created the allocation schedule with a computerized random number generator and investigators are blind to this schedule. Participants are allocated to Early Treatment with MCP using the AIMhi App, Contact Control/Delayed treatment or Treatment as usual/Delayed treatment at a ratio of 1:1:0.5. Participants are assigned a Study ID following randomisation to ensure confidentiality.

### Interventions

In addition to their allocated treatment below, all participants receive usual care from their renal service provider. The nature and extent of this care is monitored through file audits, to ensure no systematic difference between the treatment groups. Usual care is carried out according to the norms prevailing in the renal service and is informed by the needs of the client. Clinical files for each participant are carefully reviewed to examine the degree and nature of referrals or other treatment accessed over the study duration.

Either a phone (with credit) or $30 phone credit voucher is given to participants after completion of the baseline assessment and at each follow up assessment. All participants receive a text message or phone call at 10–11 weeks and 21–22 weeks post-baseline to remind them of the 3-month and 6-month assessments respectively (see Fig. 1).

#### Early treatment with MCP using the AIMhi stay strong app

##### Baseline

Participants who are randomised to the intervention complete a MCP interview of approximately 20 min duration using the AIMhi Stay Strong App (on a tablet device) at baseline, with a second 20 min session using the App within two to 4 weeks. Session 1 explores family, current strengths and worries. Participants are encouraged to set 1–2 goals that are achievable, meaningful, and practical for addressing an identified worry. The client-centred nature of the intervention ensures the goals are client driven and empowers them to take manageable steps toward achieving that goal. Session 2 reviews and refines the goals (identifies whether goals and steps were achieved) and helps clients address any barriers to goal attainment and set new goals as appropriate. Participants receive a text message or phone call 1 week following the initial treatment reminding them of their goals and steps for making changes.

